### Sub-group data analysis and handling missing data

No pre-specified subgroup analyses are planned. Both per-protocol and intention-to-treat analyses with imputation will be calculated and checked for consistency in order to assess the impact of missing data.

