**Fig. 1 Fig1:**
[figure not shown]
Schedule of enrolment, interventions, and assessments

Participants will be withdrawn from the trial and the intervention will be immediately ceased if the participant requests it, one of the exclusion criteria above is identified or violated, there is not adequate dose compliance, they experience a serious adverse event, they experience a persistent non-serious adverse event which interferes with their daily functioning, and any other condition emerges which is judged by the study team as likely to impact on the ability of the participant to complete the trial. Decisions about withdrawing participants will be made with the advice of study clinicians.

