### Randomisation, masking, and code breaking

Eligible participants will be enrolled by a masked member of the study team. A biostatistician will perform the allocation of participants to either the active intervention or placebo (in blocks of ten at a 1:1 ratio) based on a computer-generated random sequence. Only the statistician and pharmacist members of the research team and the drug manufacturer will know the identity of the drugs to be administered (see the “Drug preparation and administration” section). Unmasked team members will not interact with study participants and will not be present during any drug administration sessions. The study team will be unmasked at the completion of each randomisation block; however, the participants will not be unmasked until the full completion of the trial.

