### Strategies to improve adherence

Mobile Directly Observed Therapy (MDOT) will be used to monitor adherence to the home-dosing protocol. MDOT has been used recently in a variety of medication contexts including treatment of tuberculosis, HIV, opioid dependence, and asthma inhaler use [70]. Each dosing morning, participants will receive a text reminder with a link to upload a video of themselves self-administering. Participants will use their mobile phones to video themselves stating the date, displaying the sealed and labelled dose, then emptying the syringe into their mouth, holding their mouth closed for 30 s, and then providing a clear view of their empty mouth. Videos will be uploaded to a secure server to be checked by the study team and deleted immediately after viewing. Participants who fail to record the video correctly will be reinstructed, and those that fail to record repeatedly will be eliminated from the trial.

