### Statistical analyses and power calculations

Given the novelty of the study, there are no effect sizes on which to base power calculations. The following power sensitivity calculations were performed in G*Power 3.1 [71] using *α* = 0.05, (1-*β*) = 0.8. For independent sample *t* tests where *n* = 80, our trial will be sensitive to the effects where Cohen’s *d* = 0.56. For linear regressions, *r =* 0.37 with *n* = 40 (single group) and *r* = 0.27 with *n* = 80 (combined groups). Dropouts are anticipated; however, due to the novelty of the protocol, the rate cannot be estimated. Dropouts and other instances of missing data will be accounted for in the analysis (see the “Sub-group data analysis and handling missing data” section). In the event that there are more than ten dropouts, an extra randomisation block of participants will be added to the study and the data added to per-protocol analyses.

Questionnaires and creativity tasks will be assessed with linear mixed models with participants modelled as random factors, using baseline measurements as a covariate. Analysis of language-based creativity tasks will additionally include fluency (as measured by the NIH Picture Vocabulary Test) as a covariate. EEG LTP and MMN data will be analysed consistent with Sumner et al. [53, 54]. fMRI data will be analysed for network connectivity, inter-network connectivity, and node-based connectivity, with an additional secondary analysis of seed-based functional connectivity of the left and right amygdala. Daily questionnaire VAS data will be analysed using a linear mixed effects model. Regression analyses of any significant effects will be undertaken with genetic biomarkers, baseline MODTAS scores, change in MODTAS scores, SoS/SoP, and fMRI baseline connectivity of the DMN as predictors. Expectancy effects will be assessed by regression analysis of measure scores to a corresponding construct on a baseline expectancy questionnaire (Table 4). Due to the use of multiple primary outcome measures, the Bonferroni-Holm step-down procedure will be employed to correct for multiple comparisons where appropriate. Secondary measures will be uncorrected but considered as exploratory.

**Table 4 Tab4:** Expectancy items and corresponding measures

Expectancy item	Measures
*Do you expect that microdosing will change how ____ you feel?*	
Angry	Anger VAS
Anxious	Anxiety VAS DASS Anxiety (−) DFlex BFI-2 Negative Emotionality
Calm	Calm VAS

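### Agreement between the per-protocol and imputed intention-to-treat results cannot show that dropout has left the result unbiased, least of all for BFI-2, MODTAS and fMRI

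*Protocol article*

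**What the plan says.** The section on statistical analyses and power calculations says of dropout: "Dropouts are anticipated; however, due to the novelty of the protocol, the rate cannot be estimated". It then promises "Dropouts and other instances of missing data will be accounted for in the analysis" and refers the reader to the section on sub-group analysis and missing data. That section states one method and its purpose: "Both per-protocol and intention-to-treat analyses with imputation will be calculated and checked for consistency in order to assess the impact of missing data".

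Four other statements determine what the comparison can show:

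- **Withdrawal (Study design, below Fig. 1).** Men leave the trial, not only the treatment, if for example "there is not adequate dose compliance, they experience a serious adverse event", or if a persistent lesser adverse event interferes with daily functioning.
- **Adherence (Strategies to improve adherence).** On the dosing videos, "those that fail to record repeatedly will be eliminated from the trial".
- **Timing (Outcomes).** BFI-2, MODTAS and fMRI are taken at baseline and day 43. EEG and creativity measures also have a day-1 value.
- **Extra block (Statistical analyses and power calculations).** After more than ten dropouts, another randomisation block is recruited and its data go into the per-protocol analyses. Intention-to-treat is not mentioned there.

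**The concern.** A consistency check is useful only if its result would differ between the situation to be detected and its absence. The situation of interest here is that the men lost would have scored differently from those retained, in a way that baseline does not explain.

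The removal rules make poor compliers and dropouts largely the same men, and the article describes no day-43 assessment after withdrawal. The per-protocol set is then close to the set with day-43 data. If the missing day-43 scores are imputed from arm and baseline, the imputation uses the regression fitted to those same completers. Both analyses then share the observed data and the missing-at-random assumption, and their agreement tests neither.

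Arm-related loss is plausible in a comparison of LSD with an inactive placebo where adverse events lead to removal, although nothing in the article shows that it will occur. What is at stake is a completer bias reported as checked and found consistent.

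**Working it through.** **Inputs from the article.** 80 men, "in blocks of ten at a 1:1 ratio", so 40 per arm; baseline as covariate; block trigger at more than ten dropouts.

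**Assumed, because the article gives no figure.** Outcome SD 1; baseline to day-43 correlation r = 0.7; LSD-arm dropout 10, 20 or 30%; placebo dropout 5%; correlation 0.8 between staying in the LSD arm and the part of the outcome that baseline does not explain; no day-43 data after withdrawal.

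**The article's own figure, for scale.** It states "our trial will be sensitive to the effects where Cohen’s *d* = 0.56". With 40 per arm and power 0.80, the noncentral t gives d = 0.561 at one-sided α = 0.05 and 0.634 at two-sided. The stated value is reproduced one-sided. Sidedness is not given and does not affect this point.

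**Step 1: expected completer bias, true effect 0.** If a fraction p of the LSD arm is lost by selection with correlation ρ on the residual, the completers' mean residual is

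ρ × √(1 − r²) × φ(z) / (1 − p), where z is the upper-p normal quantile and √(1 − 0.49) = 0.714.

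- p = 0.10: 0.8 × 0.714 × 0.175/0.9 = 0.11
- p = 0.20: 0.8 × 0.714 × 0.280/0.8 = 0.20
- p = 0.30: 0.8 × 0.714 × 0.348/0.7 = 0.28

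**Step 2: does the comparison reveal it?** 1,000 simulated trials per scenario. Per-protocol is the baseline-adjusted regression in completers. Imputed intention-to-treat uses 25 multiple imputations from arm and baseline. The extra block is left out.

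| LSD-arm dropout | Per-protocol (SD) | Imputed ITT (SD) | 95% of absolute differences at most |
|---|---|---|---|
| 10%, outcome-related | 0.115 | 0.115 | 0.019 |
| 20%, outcome-related | 0.196 | 0.196 | 0.025 |
| 30%, outcome-related | 0.278 | 0.277 | 0.031 |
| 20%, unrelated | 0.006 | 0.006 | 0.027 |
| 30%, unrelated | −0.007 | −0.007 | 0.031 |

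The standard error of the effect is about 0.16 to 0.18. In the outcome-related rows the significance verdict agrees in 97 to 99% of runs. Agreement is equally close in biased and unbiased trials, so it does not separate them. The bias is 0.115/0.56 = 21% to 0.278/0.56 = 50% of the stated detectable effect.

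**Step 3: the extra block.** 20% and 5% of 40 give 8 + 2 = 10 dropouts, which is not more than ten. 30% and 5% give 12 + 2 = 14, which triggers the block, so the 30% rows describe the comparison before it is added. With the block in per-protocol only (run at 20% and 30%), the SD of the difference between analyses rises from 0.012–0.016 to 0.053–0.062. Agreement within half a standard error falls from 100% to 82–84%, with or without bias.

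**Step 4: auxiliary data in the imputation.** With 20% outcome-related dropout and an auxiliary variable correlated 0.3, 0.5 or 0.7 with the residual, the mean gap between analyses is 0.017, 0.044 or 0.095 SD. Agreement within half a standard error is 99%, 86% or 43%.

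**Step 5: what a delta shift would show.** Lowering the imputed LSD values by one residual SD moves the estimate by p × √(1 − r²): at p = 0.20, 0.2 × 0.714 = 0.14 SD (r = 0.7) or 0.2 × 0.866 = 0.17 SD (r = 0.5). Placebo-based imputation also departs from per-protocol: with a true effect of 0.56 and 20% dropout it gives 0.445 against 0.556 (dropout unrelated to outcome) or 0.614 against 0.768 (outcome-related).

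**The case against.** - **The imputation model is not stated.** Imputation from arm and baseline is an assumption here. A condensed article may leave the model, the per-protocol definition, the lead analysis and further sensitivity analyses to the SAP, and none of these is counted as missing. What remains is that the stated comparison does not serve its stated purpose under the usual imputation.
- **Only three of the seven primary measures fit fully.** AUT, RAT, LTP and MMN have a day-1 value, and daily ratings exist up to exit. Step 4 shows that strongly predictive auxiliaries can open a visible gap. This limits the point, but agreement still could not exclude dependence on the unseen outcome.
- **Per-protocol and completers are not identical.** Men with isolated lapses may stay, and under a lockdown compliant men could lack EEG or fMRI. This stands; close to the completers is as far as the text goes.
- **The size rests on assumptions.** Nothing supports a particular dropout rate or strength of selection. With 10% LSD loss and correlation 0.3, the same formula gives 0.3 × 0.714 × 0.195 = 0.04 SD (0.05 at r = 0.5). The direction is also open: the Background says absorption predicts stronger full-dose effects, so men removed for drug effects might have scored higher.

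A reader might infer that the check is bound to report consistency. The documents do not support that: the imputation method is open, and the extra block makes the two sets differ by design once dropouts exceed ten.

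**Conclusion.** The point holds in limited form: agreement between the two analyses is not evidence that dropout has left the result unbiased. It applies most directly to BFI-2, MODTAS and fMRI, if withdrawn men give no day-43 data and imputation uses arm and baseline. Under the assumed 10 to 30% outcome-related LSD-arm dropout, both analyses would show about 0.12 to 0.28 SD for a true effect of 0 and differ by no more than about 0.03 SD in 95% of trials, before any extra block. Milder assumptions shrink the bias to about 0.04 to 0.05 SD, and the opposite sign is possible.

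Disagreement is also hard to read, because beyond ten dropouts it may come from the added participants. It would be too much to conclude that an LSD benefit will be falsely declared, or that no other missing-data analysis exists: the dropout pattern is unknown and the SAP is not shown.

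**What to change.** Stop using agreement between per-protocol and intention-to-treat results as the evidence on missing data. Add a delta-adjusted (tipping-point) analysis to the imputed intention-to-treat analysis of each primary measure: shift the imputed LSD-arm values in steps, in both directions, and report the shift at which the conclusion changes. Include placebo-based imputation as one fixed case. Keep the per-protocol analysis, extra block included, as a separate question about the effect of adherent dosing.

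The cost is a wording change and a few hours of analysis. It needs no new data and no change to the withdrawal rules. The downside is a little more to report, and results that may look less robust than a plain statement of consistency.

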### Adverse event reporting and harms

Participants will be prompted to report adverse events in their daily questionnaires and to rate these events as mild, moderate, or serious. These reports will be monitored daily by members of the study team. Participant rating of any adverse event as “serious” will trigger an immediate alert to the study team to follow up with the participant. Adverse events that occur during the study visits will be recorded by the members of the study team. Events judged to be a SAE by the study team will be reported to the DSMC within 5 working days of the event and to New Zealand Medicines and Medical Devices Safety Authority (Medsafe) as per their guidelines [72].

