Resting-State fMRI	Connectivity	9-min continual recording on 3-T Siemens scanner with a 32-channel head coil.
Secondary measures		
5-Dimensional Altered States of Consciousness Questionnaire (5D-ASC) [57, 58]	Drug effects: psychological	91 items rated on VAS (1–100) with 5 scales and 11 subscales reported as % of the maximum score.
Adverse events	Unwanted health effects	Participants are asked daily to report any “unpleasant health issues” and to rate them as mild, moderate, or serious.
Consensual Assessment Technique (CAT) [59]	Creativity: non-specific	Participants are given 15 min to complete a paper collage; the result is rated by independent assessors on VAS (0–100) from low to high on (1) creativity and (2) technical goodness, reported as mean rater response.
Detail and Flexibility Questionnaire (DFlex) [60]	Attention to detail and cognitive rigidity	24 items on a 6-point scale (1–6) with 2 subscales reported as the sum of scores (total 24–144; subscales 12–72).
Daily questionnaire	Mood: well, sad, happy, stressed, creative, anxious, focused, tired, calm, connected, angry, energy, irritable, motivated, craving	15 items rated on VAS (0–100) reported as individual scores.
Depression, Anxiety, and Stress Scale (DASS) [61]	Mood: depression, anxiety, stress	42 items on a 4-point scale (0–3) with 3 subscales reported as the sum of scores (0–42).
Drug Effects Visual Analogue Scale (VAS)	Drug effects: psychological	16 items rated on VAS (0–100) reported as individual and mean scores.
Electrocardiogram (ECG)	Drug effects: physiological	QT interval, heart rate variability.
Everyday Problem-Solving Questionnaire	Creativity: problem solving	4 items rated on a VAS (0–100) reported as individual and mean scores.
Expectancy questionnaire	Expectancy	18 items rated on VAS (0–100; see Table 4).
Five Facets of Mindfulness Questionnaire (FFMQ) [62]	Mindfulness: observe, act with awareness, non-judgement, describe, non-reacting	39 items rated on a 5-point scale (1–5) with 5 subscales reported as the mean of scores.
Fitbit Charge 4, Activity and Sleep Tracker, manufactured by Fitbit, San Francisco, CA, USA	Drug effects: physiological	Activity reported as steps per day and sleep reported as minutes asleep per day.
Genetic biomarkers	Genetic	BDNF Val66Met.
Inflammatory cytokines	Immune modulation	Plasma concentration of inflammatory cytokines analysed reported in pg/ml.

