Connected to others	Connected VAS NIH Toolbox Social Satisfaction Summary BFI-2 Agreeableness BFI-2 Conscientiousness BFI-2 Extraversion
Creative	Creative VAS AUT RAT CAT Everyday problem solving
Focused	Focus VAS
Guilty	Guilt VAS
Happy	Happy VAS NIH Toolbox Psychological Well-Being Summary
Meditative	FFMQ
Motivated	Motivated VAS
Open to new experiences	BFI-2 Open-Mindedness MODTAS State of Surrender (−) State of Preoccupation 5D-ASC
Sad	Sad VAS DASS Depression
Stressed	Stressed VAS PSS DASS Stress
Well	Well VAS (−) AEs Fitbit Sleep and Activity
*Do you expect that microdosing will change how ____ you feel?*	
Craving	Craving VAS
Energy	Energy VAS (−) Tired VAS Fitbit Sleep and Activity
Self-efficacy	NIH Self-Efficacy
*Do you expect that microdosing will affect your ___*	
Cognitive functioning	NIH Toolbox Fluid Cognition Composite Score

“−” indicates negative correlation is expected

An interim analysis will be undertaken at 6-month periods for review by the Data Safety and Monitoring Committee (DSMC; see the “Data and safety monitoring” section). Interim analyses include recruitment and dropout rates, demographics, data completion, attendance and compliance, comparison of outcome measure baseline means by group, summaries of daily mood VAS ratings and vital signs, summaries of adverse events, and comparison of adverse events between the groups (see the “Adverse event reporting and harms” section). The DSMC is able to terminate the trial based on these reports.

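### The participants' adverse-event scale runs mild, moderate, serious: it has no severe grade, and its top level borrows the term the protocol uses for SAEs

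*Protocol article*

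**What the plan says.** The scale appears twice in the protocol article, with the same three levels.

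- **Adverse event reporting and harms.** Participants report events in the daily questionnaire and are asked "to rate these events as mild, moderate, or serious".
- **Outcomes, Table 3, Adverse events row (a secondary measure).** Participants are asked daily about unpleasant health issues "and to rate them as mild, moderate, or serious".

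A top-level rating has one stated consequence: it "will trigger an immediate alert to the study team to follow up with the participant". The harms section also says that the study team monitors the daily reports every day.

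SAE status is decided elsewhere: "Events judged to be a SAE by the study team will be reported to the DSMC within 5 working days of the event". The regulator is informed under its own guidelines. For events at visits, "Adverse events that occur during the study visits will be recorded by the members of the study team"; the article names no scale for these.

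In Study design, one reason for withdrawal is that "they experience a serious adverse event". A persistent non-serious event that interferes with daily functioning is listed as a separate reason.

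Under Statistical analyses and power calculations, the six-monthly reports to the DSMC include "summaries of adverse events, and comparison of adverse events between the groups". The DSMC may terminate the trial on these reports.

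**The concern.** Severity is how intense an event is. Seriousness is whether it meets the criteria for an SAE. A severe headache may be non-serious, and an event of modest intensity may meet an SAE criterion. Good practice records the two as separate items.

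Here the participant scale starts as an intensity scale and ends with a seriousness term. Two things are at stake. The first is the severity variable: a listed outcome cannot show how many events were intense. The second is the alert: it fires on the participant's choice of the word *serious*, for which the article gives no anchor. A participant who takes that word to mean something like hospitalisation may choose moderate for an event the team would want to hear about at once.

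**Working it through.** No figure in the protocol depends on this scale, so there is no stated calculation to reproduce. The check is to set the passages side by side.

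**1. Which sense does each word carry?**
- *Mild* and *moderate* are intensity words. Safety and tolerability uses them that way when it describes the headaches seen in an earlier study of older adults.
- *Serious* carries the regulatory sense in three sections. Safety and tolerability links SAEs to hospitalisation or death. Study design separates SAEs from non-serious events for withdrawal. The harms section sends SAEs to the DSMC and the regulator.
- Table 3 and the harms section agree on the three levels, so this is a stated rule and not a slip in one place.

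**2. What can a participant enter?** Cross intensity with SAE status:
- Mild or moderate, not an SAE: graded correctly.
- Mild or moderate in intensity, but meeting an SAE criterion: the participant must choose between the intensity word and the seriousness word.
- Severe, not an SAE: no matching level. It goes in as moderate (understated) or serious (misnamed).
- Severe and an SAE: *serious* fits.

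Two of the four cells are ambiguous. Comparing the participant's rating with the study team's SAE judgement resolves part of this: a *serious* rating not judged an SAE may be read as an intense non-serious event. Severe events entered as moderate cannot be separated from truly moderate ones afterwards.

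**3. Which decisions use the participant's grade?**
- Immediate alert: yes.
- Expedited SAE reporting: no; it rests on the study team's judgement.
- Withdrawal for an SAE: the text does not tie it to the participant's grade.
- Between-group comparison for the DSMC: not stated. Comparisons of any adverse event, or of SAEs, would not use the grade; a comparison by grade would.

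**4. How much rests on the self-rating?** Study design schedules visits on days 1, 14, 26 and 43. From first dose to final visit is 43 days, so 43 − 4 = 39 days have no scheduled visit. Of the 14 doses, 14 − 1 = 13 are taken at home. The daily self-report is thus the main first signal of an event, which is why its wording is worth getting right.

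**5. Can it be repaired later?** Only in part. Under Randomisation, masking, and code breaking, the study team is unmasked when each block of ten is complete. Re-grading for completed blocks could then be done by staff who know the allocation, so the grade is better captured correctly at source.

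**6. Size.** With no dropout and every prompt answered, there would be at most 43 × 80 = 3,440 daily reports from day 1 on. The article gives no rate of adverse events or of top-level ratings, so the number of blurred entries cannot be derived.

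**The case against.** The strongest reply is that the protocol keeps the two concepts apart where it matters. A participant's top rating leads only to follow-up, and the study team decides what is an SAE. All daily reports are reviewed whatever their grade, so the alert is a faster route and not the only one. The question is put to participants in lay terms. Adverse events are one secondary measure among many, and vital signs and ECG are also collected. Table layouts and grading forms normally belong in the analysis plan, the full protocol or the case report form, which are not shown.

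Most of this stands, and it rules out several stronger readings that a reader might infer:
- *That severe non-serious events cannot be recorded.* They can. They lack a label of their own, but the event is still captured, and events at visits are recorded by staff.
- *That SAE reporting is compromised.* It is protected by the separate judgement and the daily review. An SAE-type event rated moderate misses the immediate alert, but not the review.
- *That the between-arm safety comparison is distorted.* The article does not say the comparison is by grade. Both arms use the same scale, and participants are to stay masked until the trial is complete. Guessing of allocation could affect any self-rating; it does not come from this label.
- *That many ratings would be false SAE labels.* A count would need an assumed rate with no basis in the article, and a lay rating is not an SAE classification.

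The appeal to unseen documents does not remove the point. The article states the scale itself, twice, as the definition of a listed outcome. The issue is what is stated, not what is left out. Nor does the separate SAE judgement repair the severity variable or the wording on which the alert depends.

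**Conclusion.** The point holds as a minor defect in how a measurement is defined. The participant scale mixes intensity with a seriousness term, has no level for an intense non-serious event, and hangs the immediate alert on a lay reading of *serious*. Any severity breakdown built on it would be blurred, and its top row need not match the number of SAEs.

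The effect cannot be quantified from the article, and no direction of bias between arms is shown. The conclusion assumes that the questionnaire shown to participants uses the article's labels without further anchors. If the form already defines its top level by intensity, what remains is the wording in the article.

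**What to change.** - In Table 3, the harms section and the daily questionnaire, rename the top level *severe* and give each level a short functional anchor. Keep the immediate alert on the top level.
- Keep seriousness as the study team's separate judgement, and record it for each event whatever grade the participant chose.
- Tabulate severity and SAEs separately in the DSMC reports and the final report.
- Optionally, add one daily yes/no item that screens for seriousness and also raises the alert. The correction does not depend on it.

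No clinical rule needs to change. The cost is a relabel of the electronic form, slightly more tabulation and, since amendments go to the DSMC, Medsafe and the ethics committee, one small amendment. The optional item would add one question a day. Trial status describes recruitment as still to begin, which is the cheapest time to do this. If participants have already been enrolled, record which version of the form each one used, so that the two scales are not pooled unawares.
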